### MRI of the brain

MRI analyses will be performed in five hospitals on a 3 tesla MRI scanner (Philips and Siemens). During each scan session, the following sequences are acquired: 3D T1 (TE, 2.93 ms; TR, 2,300 ms; TI, 900 ms; voxel size, 1.1 × 1.1 × 1.2 mm^3^; acquisition time, 5.12 min), 3D T2 (TE, 402 ms; TR, 3,200 ms; voxel size, 1 × 1 × 1 mm^3^; acquisition time, 4.43 min), 3D FLAIR (TE, 388 ms; TR, 5,000 ms; TI, 1,800 ms; voxel size, 1 × 1 × 1 mm^3^; acquisition time, 5.52 min), DTI (32 diffusion directions, b, 800 s/mm^2^; TE, 85 ms; TR, 8,500 ms; voxel size, 2 × 2 × 2 mm^3^; acquisition time, 9.48 min). Each subject will undergo two scans (at weeks 12 and 108) at the same hospital to guarantee that both scans are made under identical conditions. An automated software algorithm will be used to detect focal MS lesions. This performs an intensity-based tissue classification using a stochastic model for normal brain images and detects MS lesions as outliers that are not well explained by the model. The T1, T2, and FLAIR images will be used as input for the lesion segmentation software. Reduction in brain parenchymal fraction (BPF) is used as a normalized measure of whole-brain atrophy. BPF is measured from the 3D T1-weighted images from each time point using a fully automated method. Diffusion tensor MRI (quantified by fractional anisotropy and apparent diffusion coefficient) will be used to assess white matter tissue integrity. To this end, all DTI datasets will be aligned to a population-specific atlas. Subsequently, diffusion parameters will be evaluated statistically in every white matter voxel. All MRI parameters will be gathered and assessed by an experienced evaluator (ICOMETRIX) who is blinded to both clinical data and treatment allocation. Because it is a secondary outcome parameter, brain MRI is not compulsory for patients having difficulty to undergo this examination.

### Sample size

The sample size was estimated on the basis of a study in untreated patients with primary progressive multiple sclerosis [23]. The primary event is sustained worsening on the T25-FW or 9-HPT within 2 years using a survival analysis. At 2 years the fraction of event-free patients is estimated to be 45% in the untreated group, and 70% in the fluoxetine-treated group. Using sample size calculation for comparing two survival curves (StatemateTM, GraphPad software, San Diego, CA, USA), including 60 patients in each group has 80% power to detect an increase in survival proportion of 0.25 with a significance level (alpha) of 0.05 (two-tailed). For every patient who drops out within the first 3 months, which is the period when we expect most drop-outs, a new patient will be included until a sample size of 120 patients is reached.

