### Study mediation, randomization, and follow-up

Eligibility of patients is determined at the screening visit (week −4). At baseline visit, patients who qualify for participation in the study are randomized 1:1 using a block size of 10, to receive either fluoxetine or placebo. Study medication (verum and placebo) was purchased from Eurogenerics and stored at the department of Pharmacy of the UZ Brussel. After inclusion, patients are given a computer-generated randomization number, which is matched to a confidential treatment number by the study pharmacist of the UZ Brussel to assign patients either to fluoxetine or to placebo.

Trained study nurses visit patients at home to perform all assessments in their natural environment, avoiding the stress and efforts of going to the hospital, which may interfere with clinical assessments. They plan the brain MRI scans, provide the study medication, and will be contacted in case of adverse events, suspected relapse, or questions. Counting tablet returns at each visit will assess adherence. In case of a suspected relapse they will refer the patient to their treating neurologist. All patients are followed as usually by their treating neurologist. When there is a change in immunomodulatory treatment or antidepressants have to be started, the treating neurologist is kindly asked to notify the study team.

Regular study visits are carried out at weeks 0, 12, 24, 36, 48, 60, 72, 84, 96, and 108. An optional follow-up visit will be offered at week 120 to confirm sustained progression appearing at week 108. If necessary, additional unscheduled visits can be performed at any time. The study flow-chart is shown in Figure 1.

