### Primary outcome parameter

The primary endpoint is the time to confirmed disease progression defined as either at least a 20% increase in the timed 25-Foot Walk (T25-FW) or at least a 20% increase in the 9-Hole Peg Test (9-HPT; assessment of upper limb function). In each situation the change cannot be attributed to another etiology (for example, fever, concurrent illness, relapse), and is sustained for at least ≥12 weeks up to the end of the trial.

In the T25-FW the patient is directed to one end of a clearly marked 25-foot course and is instructed to walk 25 feet (7.26 m) as quickly as possible, but safely. The time is calculated from the instruction to start and ends when the patient has reached the 25-foot mark. The task is immediately administered again by having the patient walk back the same distance. The score for the T25-FW is the average of the two completed trials. Patients may use assistive devices when doing this task. Because mobility may be affected by factors such as spasticity and the use of different walking aids, subsequent tests between weeks 12 and 120 will be performed with the same walking aid if any, and on the same dose of anti-spasticity medication if any.

In the 9-HPT, the patient is seated at a table with a small, shallow container holding nine pegs and a wood or plastic block containing nine empty holes. On a start command when a stopwatch is started, the patient picks up the nine pegs one at a time as quickly as possible, puts them in the nine holes, and, once they are in the holes, removes them again as quickly as possible one at a time, replacing them into the shallow container. The total time to complete the task is recorded. Two consecutive trials with the dominant hand are immediately followed by two consecutive trials with the non-dominant hand. The overall 9-HPT score is the average of the four trials.

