## Discussion

So far, no drug has been able to slow down progressive MS. Fluoxetine is mainly indicated for the treatment of mild-to-moderate depression, but the drug has potential pleiotropic neuroprotective effects [24]. The patent of fluoxetine expired in 2001. Because it is an old drug its side-effect profile, which is in general mild, is well established.

Some aspects of the trial need clarification. First, because it may take several weeks before a steady state of fluoxetine level in blood and brain is achieved [25], progression is measured from the second visit at 12 weeks, and not from start of the trial. Second, the choice of the dose of fluoxetine 40 mg is based on clinical practice indicating that dosages of 20 to 40 mg are effective in neuropsychiatric disorders. Third, the trial lasts for 2 years, because observing progression for 2 years is more meaningful than for 1 year [23]. Fourth, we decided not to use the EDSS as primary outcome measure because study nurses assess the patients in our study and the EDSS is a rather insensitive measure to assess progression. Fifth, we use cutoffs of 20% for both T25-FW and 9-HPT, because this has a better signal-to-noise ratio than lower values (for example, 15%) and is therefore preferable for the assessment of disease progression [26]. In a group of 161 primary progressive multiple sclerosis patients, Bosma and colleagues found that progression as measured with the objective outcome measures T25-FW or 9-HPT was 56% at 2 years. Combining T25-FW or 9-HPT or EDSS resulted in a slightly higher event rate of 63%. Sixth, we do not exclude patients on first-line immunomodulatory drugs (interferons and glatiramer acetate) since they have shown in clinical trials to be inefficacious in progressive MS. From a methodological point of view, a design without immunomodulatory drugs would be preferable. Because many neurologists use these drugs off-label in progressive MS we feel that excluding these patients would seriously hamper patient recruitment. The main reason for exclusion during the screening phase is the use of antidepressants, which is frequently indicated in progressive MS patients.

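### The stated 80% power assumes a full two years at risk and no loss after month 3; the endpoint rules leave 84 or 96 weeks, giving about 71–76% or 76–80% before any later loss.

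*Protocol article*

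**What the plan says.** All places are in the protocol article.

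- **Sample size.** The event and its time frame are given as "The primary event is sustained worsening on the T25-FW or 9-HPT within 2 years using a survival analysis". The inputs are: "At 2 years the fraction of event-free patients is estimated to be 45% in the untreated group, and 70% in the fluoxetine-treated group". The conclusion is that "including 60 patients in each group has 80% power to detect an increase in survival proportion of 0.25", at two-sided alpha 0.05. Patients lost in the first 3 months are replaced until 120 is reached. The text expects most, not all, losses in that period. It gives no rate and no inflation for later loss.
- **Discussion.** Because the drug takes weeks to reach steady state, "progression is measured from the second visit at 12 weeks, and not from start of the trial".
- **Primary outcome parameter.** The worsening must be "sustained for at least ≥12 weeks up to the end of the trial".
- **Study mediation, randomization, and follow-up.** Regular visits are 12 weeks apart from week 0 to week 108. Beyond that, "An optional follow-up visit will be offered at week 120 to confirm sustained progression appearing at week 108".

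**The concern.** The sample-size paragraph and the endpoint definition use different lengths of time at risk. The 45% and 70% are two-year figures, about 104 weeks. By the endpoint rules the clock starts at week 12, and a worsening first seen at week 108 counts only if the patient takes an optional extra visit. The countable onset window is then weeks 12 to 96, or weeks 12 to 108 for those who attend week 120. A shorter window at the same hazards gives fewer events, and log-rank power depends on events.

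Replacing early drop-outs does not help here, because the first 3 months end about when the counted window opens. Loss inside the window has no allowance.

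The 80% is the only power figure in the article. If the trial finds no difference, readers will use it to judge how strongly that result speaks against an effect of the planned size.

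**Working it through.** **Inputs.** From Sample size: 60 per arm, event-free 0.45 and 0.70 at 2 years (104 weeks), two-sided alpha 0.05 (z = 1.96). From the visit schedule and endpoint rules: window of 96 − 12 = 84 weeks, or 108 − 12 = 96 weeks. Assumed here because the article does not give them: constant hazards, and late loss of 0%, 10% or 20% over the window (exponential).

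**Step 1: reproduce the stated figure.**
- Hazard ratio: HR = ln(0.70)/ln(0.45) = 0.447.
- Expected events, no loss: 60 × (0.55 + 0.30) = 51.
- Schoenfeld: Φ(½·√51·|ln 0.447| − 1.96) = 82.1%.
- Freedman: Φ(√51·(1 − 0.447)/(1 + 0.447) − 1.96) = 78.0%.
- Two proportions, 60 per arm: 79.9%.
- Simulated log-rank, 3,000 runs: 80.9%.

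So 80% is right for 104 weeks with everyone followed.

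**Step 2: scale to the countable window.** Under constant hazards, S(T) = S(104)^(T/104).
- T = 84: 0.45^(84/104) = 0.525 and 0.70^(84/104) = 0.750, a difference of 22.5 points. Events: 60 × (0.475 + 0.250) = 43.5.
- T = 96: 0.479 and 0.719, a difference of 24.0 points. Events: 48.1 (from unrounded rates).

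**Step 3: power at HR 0.447, no later loss.** The simulations for the two windows use the 12-weekly visit grid.

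| Window | Events | Freedman | Two proportions | Schoenfeld | Simulated log-rank |
|---|---|---|---|---|---|
| 104 weeks | 51.0 | 78.0% | 79.9% | 82.1% | 80.9% |
| 96 weeks | 48.1 | 75.6% | 77.5% | 79.8% | 78.7% |
| 84 weeks | 43.5 | 71.4% | 73.3% | 75.8% | 75.6% |

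**Step 4: add late loss (assumed).** With dropout rate g = −ln(1 − loss)/T, expected events per arm are 60·λ/(λ + g)·(1 − e^(−(λ+g)T)), where λ is that arm's hazard.

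| Window | Loss | Events | Freedman to Schoenfeld |
|---|---|---|---|
| 96 weeks | 10% | 45.9 | 73.6–77.9% |
| 96 weeks | 20% | 43.6 | 71.4–75.8% |
| 84 weeks | 10% | 41.5 | 69.3–73.8% |
| 84 weeks | 20% | 39.4 | 67.0–71.5% |

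By formula, the cost of late loss is about 2 points at 10% and 4 points at 20%.

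**Step 5: what if the source rate already includes confirmation?** If the cohort's two-year rate required 12 weeks' confirmation inside the two years, its onset window was 104 − 12 = 92 weeks. Fixing 45% and 70% at 92 weeks, with no loss:
- 84 weeks: 47.7 events, power 75–80% (Freedman 75.3, two proportions 77.2, Schoenfeld 79.5).
- 96 weeks: 52.6 events, power 79–83%.

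**The case against.** The strongest reply has three parts.

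1. **The 96-week window is the intended one.** The week-120 visit exists to confirm onset at week 108, the walking-test rules cover visits up to week 120, and nurses visit at home, so attendance may be high. The two windows differ by only 48.1 − 43.5 = 4.6 events. This stands in part. It makes 84 weeks the lower bound rather than the expected case. But the visit is optional, so the plan does not secure the longer window.

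2. **The confirmation period may be deducted twice.** The article describes the event behind 45% and 70% as sustained worsening within 2 years. If the cohort's rate was already a confirmed one, Step 5 applies and the 96-week case has no shortfall. The article does not say how the cohort's events were confirmed, so this stands as an open condition on the result.

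3. **The gap is about the size of the spread between formulas** (78–82% at 104 weeks). That is fair for the 96-week case. Within any one formula, though, the loss is consistent: about 2 points at 96 weeks and 6–7 points at 84 weeks.

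A reader might also infer a flat figure for delivered power, such as 68–75%. The documents do not support that. Its low end needs both no attendance at week 120 and about 20% late loss, a rate the article nowhere gives. It also leaves out the case of full week-120 attendance and little loss, where power is close to target.

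**Conclusion.** The point holds as a mismatch of inputs, not as an arithmetical error. The stated power belongs to a 104-week risk period with complete follow-up. On a plain reading of the endpoint rules and without later loss, it is about 71–76% if onset at week 108 goes unconfirmed and about 76–80% if all needed week-120 visits happen. Partial attendance falls between. An assumed 10–20% late loss lowers these by about 2–4 points.

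The figures rest on constant hazards, on the planned hazard ratio of 0.447, and on 45% and 70% referring to onset over 104 weeks. If they refer instead to events confirmed within two years, the 84-week figure rises to 75–80% and the 96-week figure to 79–83%. The shortfall is therefore modest, and its exact size cannot be settled from the article. The article does not show that the 80% applies to the window actually used.

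**What to change.** Keep 120 patients and rewrite the Sample size paragraph for the onset window the endpoint rules create:

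- Replace the 2-year period by the week 12 to 96 window, extended to week 108 for patients confirmed at week 120.
- Give the event-free rates scaled to that window (52.5% versus 75.0% over 84 weeks; 47.9% versus 71.9% over 96 weeks) and the expected events (43.5 and 48 before loss).
- State an explicit assumption for loss after week 12, and reduce the expected events accordingly.
- Say whether the source cohort's two-year rate already required confirmation within the two years. If it did, use the Step 5 figures.
- Report the resulting power, or the larger effect for which 80% holds. For 84 weeks without loss that effect is a hazard ratio of about 0.43 by Schoenfeld: the fluoxetine event-free rate is 0.525^0.425 = 0.760, events are 60 × (0.475 + 0.240) = 42.9, and ½·√42.9·|ln 0.425| = 2.80 = 1.96 + 0.84.

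The cost is rewording and a stated power that is slightly less favourable. No extra patients are needed.

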### Blinding and statistical methods

Patients and the entire study staff will remain blinded throughout the complete treatment period. Treatment allocations will only be disclosed after the final database lock. Independent examiners will do MRI and OCT evaluations. All data will be statistically analyzed by an independent biometrician. Proportion of patients will be analyzed with the use of a chi-square test. A log-rank test will be applied to compare differences in time to confirmed disease progression between the two treatment groups. A Cox proportional hazard model will be used to estimate the reduction in hazard associated with treatment compared with placebo. Repeated measures analysis of covariance will be used to compare differences between the fluoxetine and placebo group in endpoints related to changes from baseline. The test level for statistical significance of differences between both treatment arms is defined as *P* = 0.05 for all tests.

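### The primary log-rank test is valid and reaches its planned power, but the article names no baseline adjustment, so a possible gain in power at 60 patients per arm is forgone

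*Protocol article*

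**What the plan says.** The section on blinding and statistical methods gives the primary comparison as "A log-rank test will be applied to compare differences in time to confirmed disease progression between the two treatment groups". The effect estimate follows: "A Cox proportional hazard model will be used to estimate the reduction in hazard associated with treatment compared with placebo". Neither sentence names a stratum or covariate. In the same paragraph the change endpoints do get covariance adjustment: "Repeated measures analysis of covariance will be used to compare differences between the fluoxetine and placebo group in endpoints related to changes from baseline".

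The section on randomization and follow-up says that patients are "randomized 1:1 using a block size of 10" and names no stratification factor. Under Sample size, "the fraction of event-free patients is estimated to be 45% in the untreated group, and 70% in the fluoxetine-treated group", and "including 60 patients in each group has 80% power to detect an increase in survival proportion of 0.25", at a two-sided 5% level.

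The Participants section admits secondary and primary progressive MS with EDSS from 3 to 6.5, and allows interferon beta or glatiramer acetate. Eligibility therefore requires an EDSS score and an MS type for every patient. Study visits begin at week 0, but the text does not list the tests done at each visit, and the flow chart (Figure 1) is not shown.

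**The concern.** About 51 events are expected in a population with a wide range of disability. If entry disability predicts who worsens by 20%, a comparison that leaves it out has less power than one that includes it. A chance difference between the arms in that factor also passes into the primary result uncorrected. The log-rank test is a named choice and not a detail left open, and at least EDSS is already in hand, so a more efficient analysis would need no new patients. The design also has little power in reserve: patients who drop out in the first three months are replaced, but the sample size section describes no allowance for later losses.

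**Working it through.** **Inputs from the article.** Event-free at 2 years: 45% versus 70%; 60 per arm; two-sided alpha 0.05; 80% power.

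**1. The plan's own figure.**
- Hazard ratio = ln(0.70)/ln(0.45) = 0.447, so log HR = -0.81. Mean event probability = (0.55 + 0.30)/2 = 0.425. Expected events = 120 × 0.425 = 51.
- Schoenfeld: events = 4(1.96 + 0.84)²/(log HR)² gives 49. Then 49/0.425 = 115.3 patients, or 58 per arm. Power with 51 events is 82.1%.
- Freedman: 54 events, 64 per arm; power with 51 events is 78.0%.
- Two proportions without continuity correction: 61 per arm; power at 60 per arm is 79.9%.

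The stated 60 per arm reproduces, with power of 78.0% to 82.1% and no adjustment.

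**2. What adjustment could add.** The documents give no prognostic strength, so a range is assumed. Both simulations use 60 per arm and the planned 45% versus 70%.
- Simulation A: one standard normal covariate, exponential times, censoring at 2 years, no dropout, marginal survival held at 45% and 70%, 4,000 runs (Monte Carlo error about 0.6 points).
- Simulation B: a Cox model with four covariates and 12-weekly visits.

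| Log-hazard SD (assumed) | HR per SD | A: log-rank vs adjusted Cox | B: unadjusted vs adjusted |
|---|---|---|---|
| 0 | 1.00 | 80.5% vs 79.2% | 78% vs 77% |
| 0.2 | 1.22 | 81.0% vs 80.5% | not run |
| 0.3 | 1.35 | 81.8% vs 82.4% | 80% vs 80% |
| 0.5 | 1.65 | 79.9% vs 84.4% | 80% vs 84% |
| 0.7 | 2.01 | 82.4% vs 89.4% | not run |
| 0.8 | 2.2 | not run | 83% vs 91% |
| 1.0 | 2.72 | 82.6% vs 94.5% | 80% vs 93% |

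Unadjusted power stays near 80% in every row; only the adjusted column moves.

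**3. Type I error.** With no treatment effect, the unadjusted log-rank test rejected in 4.3% to 5.6% of runs in A (2,000 runs per setting). The adjusted Wald test rejected in 4.2% to 6.1% in A and 5.0% to 5.6% in B.

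**4. Chance imbalance.** The standardised difference in a baseline covariate has SD = √(2/60) = 0.183. Hence P(|d| > 0.25) = 17% and P(|d| > 0.36) = 5%. A difference of 0.36 in a covariate with HR 1.35 per SD (log HR 0.30) shifts the treatment log HR by about 0.36 × 0.30 = 0.11, against the design value of -0.81. For a binary factor with an assumed prevalence of 30%, the exact binomial chance of a gap above 10 percentage points is 19.5%. If that factor doubled the hazard, a 10-point gap would shift the log HR by roughly 0.10 × ln 2 = 0.07.

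**The case against.** The strongest objection is that nothing here is wrong. The log-rank test is standard, keeps its type I error, and matches the method used to size the trial. All of that stands.

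A reader might infer that the plan loses power. The documents do not support this: the planned 80% is met without adjustment, and what is missed is a possible gain.

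A reader might also infer that randomisation is unstratified and that the Cox model contains treatment alone. Both readings come from silence. The article neither lists nor excludes covariates or strata, and a condensed article may leave them to the full protocol or analysis plan. What remains is that the primary test is named, and named without adjustment.

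To say that baseline disability is ignored would also go too far. The event is a 20% rise over the patient's own earlier T25-FW or 9-HPT value, so the starting level sets the threshold. Risk may still depend on that level, or on EDSS, but the documents do not show that it does.

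The Background section says that secondary and primary progressive disease advance at similar rates, which weakens the case for MS type as a covariate. The article also holds that interferon and glatiramer do not slow progression, so it gives no ground for adjusting for them.

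Finally, with a non-collapsible measure such as the hazard ratio, adjustment changes the quantity estimated. The unadjusted ratio corresponds to the marginal 45% versus 70% contrast; the adjusted one is conditional on the covariates. This is a real cost in interpretation and a reason to keep both.

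**Conclusion.** The point holds as a modest efficiency recommendation. As written, the primary test is unadjusted, and it is valid at about 80% power. Adjustment for a few pre-treatment values would change power by between about -1 and +13 points, depending wholly on a prognostic strength that the documents do not give. With weak covariates there is practically nothing to gain; a material gain needs a combined prognostic effect of about HR 1.65 per SD or more.

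Chance imbalance is a secondary argument. It does not inflate the type I error of the log-rank test, and the shifts worked out above are small beside the design effect. The sizes rest on the simulation assumptions: normally distributed prognostic values, the planned event rates and, in Simulation A, no dropout.

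**What to change.** Before unblinding, name as the primary test the treatment effect in a Cox model with Efron handling of ties (12-weekly assessments will produce ties). Adjust for entry EDSS and, if both timed tests are done at week 0, for log T25-FW and log 9-HPT. MS type is optional. Use week-0 and not week-12 values, because week 12 falls after treatment has started and could already reflect its effect. State the covariates and their functional form in advance. Report the unadjusted log-rank test and hazard ratio as supportive.

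Even with MS type included, the model has five parameters on about 51 expected events, which is adequate. The cost is a wording change with no new data, provided that the week-0 tests exist. The price is up to about one point of power if the covariates turn out not to be prognostic, and a primary hazard ratio that is conditional and not marginal. If the full protocol or analysis plan already specifies such an adjustment, it is enough to make the primary test agree with it.
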